### Procedures for randomization

2.4

An independent statistician will prepare the randomization list in SAS version 9.1.3 (SAS Institute Inc., Cary, NC, United States), using a fixed seed to ensure reproducibility. At visit 1, eligible participants—those satisfying the inclusion and exclusion criteria—will be assigned to either the herbal medicine or standard traditional Korean medicine (TKM) group through block randomization with a 1:1 ratio. Each participant will receive a site-specific enrollment number and a randomization code delivered via sealed envelopes handled by an external party. During screening, investigators will secure informed consent, document eligibility, and issue consecutive screening codes (e.g., S1-01). Once eligibility and consent are verified, participants will be enrolled and given a unique allocation code (e.g., R1-01) linked to the randomization schedule.

This open-label study maintains assessor blinding: outcome evaluators (research nurses or residents), who neither provide treatment nor know group assignments, will perform assessments in isolated rooms. Items at risk of unblinding—such as credibility/expectancy scales, cost records, medication logs, and adverse event reports—are exempt from this blinding.

### Interventions

2.5

This pragmatic randomized controlled trial will assign participants to either the herbal medicine or TKM treatment group. The specific methods for both herbal medicine and typical TKM interventions will not be predefined; instead, they will be determined by the clinician’s judgment based on the patient’s individual condition and progress, with all administered interventions meticulously recorded in case report forms (CRFs).

#### Herbal medicine

2.5.1

This strategy focused on evaluating the effectiveness of herbal medicines. The type of herbal formula and its administration will be selected from those commonly prescribed for lumbar intervertebral disc herniation in acupuncture and moxibustion textbooks of TKM (18). Dosage instructions will be provided by the clinician and details such as formula type, administration frequency, and pack volume will be recorded. Herbal medicines are prepared at the institution’s dispensary for patient pickup or delivery. Compliance will be monitored weekly, and at week 7, the total number of prescribed and remaining packages will be counted. Participants in this group will take herbal medicines orally for 30 days, with clinic visits every 10 days for follow-ups and new prescriptions, totaling three 10-day prescriptions.

#### Usual traditional Korean medicine treatments

2.5.2

This strategy employs a combination of traditional Korean medicine (TKM) therapies for lumbar intervertebral disc herniation, selected by a Korean medical doctor based on patient symptoms and progress. Modalities include acupuncture (e.g., BL23, BL25, GV3, GV4, BL32, BL40, BL60, GB30, GB34, SP6 for 15 min), electroacupuncture (BL23, BL25 for 15 min at 3 Hz), transcutaneous infrared irradiation, bloodletting cupping (L1-L5 for 5 min), moxibustion (43 ± 1 °C on two acupoints for 15 min), and physical therapy (ICT or TENS for 10–15 min). Treatments occur twice weekly for 5 weeks, adjustable to 1–3 times per week based on patient needs, with a maximum of 10 sessions. All treatment details are recorded.

#### Concomitant therapy

2.5.3

To ensure that the study reflects real-world clinical practice, there will be no restrictions on concomitant therapies for LBP or radiculopathy symptoms during the study period. All concurrent treatments were fully documented for accurate evaluation.

### Outcome measures

2.6

This study used a comprehensive set of outcome measures to evaluate the effectiveness and safety of the interventions. All patient-reported outcomes were assessed at specific visits throughout the study.

(1) NRS scores for pain intensity (low back and radicular pain).

At weeks −1 (baseline), 0, 3, 5, 7, 12, 19, and 26, participants will assess their low back pain and radiating leg pain over the past week using an 11-point Numeric Rating Scale (NRS), ranging from 0 (no pain) to 10 (worst pain imaginable), selecting the number that best reflects their current discomfort level.

(2) Oswestry disability index.

At weeks 0, 3, 5, 7, 12, 19, and 26 visits, participants will complete the ODI (19) questionnaire by providing answers to each question.

(3) VAS score for pain intensity (low back and radicular pain)

At weeks 0, 7, 12, 19, and 26, participants will use a 100 mm Pain Visual Analog Scale (VAS) (20) to quantify their LBP experienced over the past week. Participants will indicate their current pain level by marking a point on a 100 mm Visual Analog Scale (VAS), ranging from “no pain” to “worst pain imaginable”.

(4) Roland-Morris disability questionnaire (RMDQ)

At weeks 0, 7, 12, 19, and 26, the participants will complete the Roland-Morris Disability Questionnaire (RMDQ) (21) by answering each question.

(5) EuroQol-5 dimension-5 level (EQ-5D-5L)

At Weeks 0, 3, 7, 12, 19, and 26, the participants will complete the EQ-5D-5L (22) questionnaire by responding to each question.

(6) Health-related quality of life instrument with eight items (HINT-8)

At weeks 0, 3, 7, 12, 19, and 26, participants will complete the HINT-8 questionnaire (23). Participants will assess their health status over the past week by selecting one of four response levels for each question, ranging from 1 (e.g., “not at all” for climbing stairs or “not at all depressed” for depression) to 4 (e.g., “unable to climb” or “always depressed”).

(7) Global perceived effect (GPE)

At weeks 3, 7, 12, 19, and 26, participants completed the Global Perceived Effect (GPE) questionnaire (24) by providing answers to each question.

(8) Patient health questionnaire-15 (PHQ-15)

At weeks 0, 7, 12, 19, and 26, participants will complete the Korean version of the Patient Health Questionnaire-15 (PHQ-15). This tool, a 15-item condensed version (25) developed by Kroenke et al. from Spitzer et al.’s PHQ (26), assesses general health status and subjective somatic symptoms.

(9) Kidney Yin deficiency pattern identification questionnaire score (DSKI)

At weeks 0 and 7, participants will complete the Kidney Yin Deficiency Pattern Identification Questionnaire (DSKI) (27) to assess the Kidney Yin Deficiency Pattern, a diagnostic construct in Korean traditional medicine characterized by symptoms such as lower back pain, fatigue, night sweats, dry mouth, and insomnia, reflecting an imbalance in yin energy essential for bodily nourishment and cooling. The DSKI quantifies these symptoms through a standardized set of questions, with scores indicating the severity of the deficiency pattern. This measure is relevant to the study as it evaluates the impact of traditional alternative therapies on a key diagnostic pattern associated with lumbar disc-related radiating pain.

(10) Intention to choose herbal medicine.

At weeks 0 and 7, participants were asked about their perceived need for herbal medicine treatment in their current condition.

(11) Treatment expectation scale.

At the initial visit, participants will rate their expectations of symptom relief from herbal medicine and acupuncture treatments on a 9-point Likert scale (1 = not at all, 5 = somewhat, 9 = very much).

### Statistical analysis

2.7

Data will be analyzed using intention-to-treat (ITT) and per-protocol (PP) sets. The ITT population includes all randomized participants receiving at least one dose of herbal medicine or one traditional Korean medicine (TKM) session. The PP population comprises ITT participants with ≥70% herbal medicine compliance or ≥7 TKM sessions. Efficacy outcomes will be assessed in both ITT and PP populations, with ITT as the primary analysis and PP as supportive. Demographic and safety evaluations will use the ITT population, with safety analyses based on raw data without imputation. Statistical analyses will be conducted using SAS version 9.4 (SAS Institute, Cary, NC, United States) with a two-sided significance level of 0.05 and 95% confidence intervals.

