This investigation is designed as a pragmatic randomized controlled trial (PRCT) to provide information relevant to decision-making in real-world clinical practice. Unlike explanatory clinical trials, which are typically conducted for drug approval and assess the efficacy of an intervention under ideal conditions, PRCTs evaluate the “overall effectiveness” of a treatment in routine clinical settings (12). It is crucial to understand that PRCTs are not alternatives to traditional randomized clinical trials (RCTs) but rather extensions of explanatory trials (13). Guidelines such as the CONSORT extension checklist and the pragmatic-explanatory continuum indicator summary (PRECIS)-2 are recommended for reporting and evaluating PRCTs (14). A key characteristic of PRCTs is their reflection of actual clinical environments, indicating that treatments and interventions adhere to usual clinical practice, and management methods maintain the same level as real-world care (15).

Numerous clinical studies have adopted this research design, with a notable example being a trial comparing surgical strategies with intensive rehabilitation in patients with chronic LBP. In this study, the PRCT design allowed the use of various surgical methods applicable at each site, determined at the physician’s discretion, without predefining the surgical approach (16). PRCTs are particularly appropriate for evaluating the comparative effectiveness of herbal medicine in treating LIDH, as they enable assessment of interventions under routine clinical conditions and facilitate comparisons where placebo controls are ethically or practically challenging. Despite differences between the experimental arm (herbal medicine, involving daily oral administration) and the control arm (acupuncture, moxibustion, and blood-letting cupping, delivered in periodic sessions), these variations align with standard TKM practice, in which treatment modalities are tailored to individual patient needs and clinical discretion, thereby strengthening the study’s external validity and real-world relevance. To safeguard internal validity and enhance interpretability, the analysis will employ intention-to-treat principles, covariate adjustment for baseline imbalances, sensitivity tests for adherence and frequency variations, and subgroup analyses to explore the influence of modality-specific factors on outcomes, yielding a rigorous and transparent comparison of treatment effects.

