	Anthropometric measurements	●												●			
	Concomitant medication review^8^	●	●					●				●		●	●	●	●
	Adverse effect assessment^9^			●		●		●		●		●		●	●	●	●
Treatment compliance assessment^10^				▲^11^		▲^11^		▲^11^		▲^11^		▲^11^		▲^11^			
Experimental group^11^			■		■ (10D)			■ (20D)									
Control group^12^				▲	▲	▲	▲	▲	▲	▲	▲	▲	▲				

1 Follow-up visits at weeks 12, 19, and 26 may be conducted via telephone surveys if in-person visits are impractical. In such cases, vital signs and VAS measurements were omitted.

2 Missing follow-up questionnaires (including telephone surveys) due to a participant’s missed visit will not be considered a protocol violation.

3 For the experimental group, weeks −1 and 0 visits were conducted on the same day. For the control group, weeks −1, 0, and 1–1 visits can were conducted on the same day.

4 Lumbar spine CT or MRI examination results, whether performed at the current institution or other hospitals, may be used if previously acquired.

5 At week 3, the assessment of the NRS, VAS, ODI, EQ-5D-5L, HINT-8, GPE, healthcare utilization costs/time survey, time–cost evaluation, productivity loss, and vital signs may have been conducted concurrently with the day 20 visit for the intervention group. For the control group, these assessments will be performed at week 3–1, or week 3–2 if not completed at week 3–1.

6 NRS, ODI assessments, and medical cost surveys at week 5 will be conducted via telephone survey.

7 Participants will undergo blood and urine tests at weeks −1 and 7. They would be required to visit after an 8-h fasting period on the day prior to blood collection for the tests. Retesting for abnormal results may be performed at the discretion of the investigator. However, for week −1 clinical laboratory tests, the results from tests conducted within 14 days of the screening visit can be substituted. The specific test items were as follows: (a) blood test items: WBC, RBC, neutrophils, lymphocytes, monocytes, eosinophils, basophils, MCV, MCH, MCHC, hemoglobin, hematocrit, platelet count, total protein, albumin, ALT, AST, ALP, total bilirubin, gamma GT, uric acid, BUN, creatinine, BUN/creatinine ratio, serum glucose, PT, aPTT, ESR, and CRP. (b) Urine Test Items: specific gravity, pH, protein, glucose, ketones, urobilinogen, bilirubin, blood, nitrite, WBC (leukocytes). For female participants, urine HCG screening was performed at week −1.

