### Dropout and withdrawal

2.8

Participants may withdraw voluntarily at any point or be removed by the investigator, with the main reason recorded. Those exiting before treatment begins count as screening failures and, barring medical need, need not complete discontinuation evaluations. Withdrawals due to adverse events (AEs) will receive suitable care, and monitoring will persist for intervention-related AEs until resolved or stabilized. Exclusion criteria include: (1) participant or legal representative requesting withdrawal or revoking consent; (2) newly identified conditions impacting study results; (3) major breaches of inclusion/exclusion rules; (4) confirmed pregnancy; (5) a serious AE necessitating withdrawal or making involvement impractical; (6) barriers to conducting medical or traditional Korean medicine (TKM) procedures for lumbar disc herniation; (7) investigator judgment that ongoing participation is unsuitable; or (8) herbal medicine adherence below 70% across 5 weeks or fewer than six usual care sessions attended. Follow-up assessments may proceed with consent after treatment ends.

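### The primary 'ITT' set leaves out randomised participants who never start treatment, so it is a modified ITT set and could bias an open-label comparison

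*Protocol article*

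**What the plan says.** Section 2.7 (Statistical analysis) of the protocol article defines the set: "The ITT population includes all randomized participants receiving at least one dose of herbal medicine or one traditional Korean medicine (TKM) session". Efficacy is analysed "with ITT as the primary analysis and PP as supportive". The per-protocol set is a subset of this one, and demographic and safety evaluations use it too. The article defines no set of all randomised participants.

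Section 2.4 (Procedures for randomization) places allocation at visit 1, where eligible participants enter a "group through block randomization with a 1:1 ratio". The same section states: "This open-label study maintains assessor blinding".

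Treatment follows allocation. In the herbal arm, section 2.5.1 says: "Herbal medicines are prepared at the institution’s dispensary for patient pickup or delivery". In the control arm, Table 1 puts the first session at V2 (week 1), and its footnote 3 permits but does not require an earlier start: "For the control group, weeks −1, 0, and 1–1 visits can were conducted on the same day".

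Section 2.8 (Dropout and withdrawal) adds: "Those exiting before treatment begins count as screening failures and, barring medical need, need not complete discontinuation evaluations".

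The Background, listing the safeguards of internal validity, says that "the analysis will employ intention-to-treat principles". The Discussion names intention-to-treat analysis among the features that offset the biases of the open-label format.

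**The concern.** Intention-to-treat protects a comparison because membership of the analysis set is fixed at randomisation and cannot depend on anything that happens later. The set in section 2.7 depends on a later event: whether the participant took a dose or attended a session. In a blinded trial that condition is easier to defend, because the arm cannot drive the decision to start. Here participants know their arm first, and the arms differ in kind: daily oral medicine against repeated clinic procedures.

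If people who decline to start differ in prognosis from those who start, and if declining is more common in one arm, the primary comparison of week-7 change in radiating-pain NRS and ODI is no longer between the groups that were randomised. Section 2.8 adds to this. It does not separate exits before randomisation from exits between randomisation and first treatment, and it waives discontinuation evaluations for both. Outcome data that would allow a full intention-to-treat analysis may then never be sought.

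**Working it through.** **Step 1. The passages side by side.**

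| Event | Place in the article | Consequence |
|---|---|---|
| Randomised at visit 1, arm known | 2.4 | Has an allocation code |
| First herbal dose, or first session at V2 (same day optional) | 2.5.1; Table 1, footnote 3 | May fall after the randomisation visit in either arm |
| Leaves before that first treatment | 2.7 | Outside 'ITT', hence also outside PP |
| Same person | 2.8, as worded | Can be counted as a screening failure; discontinuation evaluations waived |
| Stated protection | Background; Discussion | Intention-to-treat |

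The last row does not agree with the third.

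**Step 2. Inputs for the size.**
- Arm size 37, from section 2.3. Table 2 reproduces it: 33 / (1 − 0.10) = 36.7, rounded up to 37.
- Planned difference 5 points, SD 10 points, from section 2.3. I read these as ODI points, since an SD of 10 cannot belong to a 0-to-10 NRS.
- Number of never-starters k, and their outcome gap g from starters: not in the documents. Both are assumed and shown as ranges.

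**Step 3. Formula.** Let f = k/37, m_s the mean change of starters and m_n that of never-starters.
- All-randomised arm mean = (1 − f) × m_s + f × m_n
- Treated-set arm mean = m_s
- Shift = m_s − [(1 − f) × m_s + f × m_n] = f × (m_s − m_n) = (k/37) × g

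The bias in the between-arm difference is the shift in one arm minus the shift in the other. Equal k and equal g in both arms cancel.

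**Step 4. Results, never-starters in one arm only.**

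| k | Share of arm | ODI shift, g = 5 / 10 / 15 | NRS shift, g = 1 / 2 / 3 |
|---|---|---|---|
| 0 | 0% | 0 / 0 / 0 | 0 / 0 / 0 |
| 1 | 2.7% | 0.14 / 0.27 / 0.41 | 0.03 / 0.05 / 0.08 |
| 2 | 5.4% | 0.27 / 0.54 / 0.81 | 0.05 / 0.11 / 0.16 |
| 3 | 8.1% | 0.41 / 0.81 / 1.22 | 0.08 / 0.16 / 0.24 |
| 4 | 10.8% | 0.54 / 1.08 / 1.62 | 0.11 / 0.22 / 0.32 |

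**Step 5. Scale.** For k = 3 and g = 10, 0.81 / 5 = 16% of the planned difference; for k = 4, 1.08 / 5 = 22%. The standard error of the difference with 33 per arm is 10 × √(2/33) = 2.46, so these shifts are 0.81 / 2.46 = 0.33 and 1.08 / 2.46 = 0.44 standard errors.

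**The case against.** The strongest reply is that the fault may be little more than a label, and that larger claims go beyond the text. Most of this stands.

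- **Screening failures.** A reader might infer that the protocol deliberately reclassifies randomised people. Section 2.8 never uses the word randomised, and it also covers exits during screening, for whom the term is right. What stands is that the wording does not exclude post-randomisation exits, and that section 2.7 removes them from the primary set in any case.
- **Hidden losses.** A reader might infer that non-starters vanish from the participant flow. The documents do not support this. Section 2.4 gives each enrolled participant an allocation code distinct from the screening code, and section 2.8 requires the main reason for withdrawal to be recorded, so non-starters stay countable. The flowchart is not available to check.
- **No further evaluation.** Section 2.8 waives discontinuation evaluations only. It does not bar collecting week-7 NRS or ODI.
- **Preference.** It is tempting to say that people will leave because they did not get the arm they wanted. The preference the article cites is for traditional Korean medicine in general, and both arms are of that kind. Measuring expectation and intention at baseline does not show that anyone refuses an allocation.
- **Longer wait in the control arm.** This cannot be established. Footnote 3 allows a same-day first session, and pickup or delivery can delay the first herbal dose.
- **Size.** Three or four never-starters in one arm would use most or all of the 37 − 33 = 4 losses per arm that Table 2 allows. A gap of 10 ODI points is twice the planned difference, and the calculation assumes no offsetting loss in the other arm.
- **Gain from redefinition.** A non-starter with no post-baseline value adds little to a mixed model for repeated measures. This is correct, and it is why the fix must include seeking outcomes.

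None of this removes the core point: the primary set depends on a post-randomisation event in an unblinded trial that claims intention-to-treat protection.

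**Conclusion.** The point holds in a limited form. The set called ITT is a modified ITT set, no all-randomised set is defined, and this conflicts with the protection claimed in the Background and Discussion. Section 2.8 is loose enough to treat post-randomisation non-starters as screening failures.

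The consequence is a possible bias, not a demonstrated one. It needs never-starters whose number or outcome gap differs between the arms. Under assumed values of 2 to 4 never-starters in one arm and a gap of 5 to 15 ODI points, that arm's mean shifts by 0.27 to 1.62 points against a planned difference of 5. It is zero if everyone starts. The documents therefore do not show that the randomised comparison is broken.

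It is still worth correcting now. Section 2.2 says that recruitment is under way, and week-7 outcomes that are not sought cannot be recovered later.

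**What to change.** 1. In section 2.7, define ITT as all randomised participants analysed in the arm assigned, and use it for the primary efficacy analysis.
2. Keep the present definition under another name, as the treated or safety set. Safety evaluations, which now use the ITT population, should then refer to it.
3. In section 2.8, limit screening failure to exits before randomisation.
4. Seek week-7 NRS and ODI from randomised participants who do not start and who consent to contact, by telephone if needed. Table 1, footnote 6 already uses the telephone for both measures at week 5. Without these data, the new definition adds little under the planned mixed model.
5. Report non-starters by arm.

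The cost is a few sentences in sections 2.7 and 2.8 and a few extra follow-up calls, some of which will fail because the person has withdrawn. Including non-starters may also dilute the estimated effect slightly.

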#### Analysis of efficacy endpoints

2.7.2

1) Primary efficacy endpoint

Changes in Numeric Rating Scale (NRS) for radiating pain and Oswestry Disability Index (ODI) from baseline to week 7 will be analyzed using a Linear Mixed Model, with group as a fixed factor and relevant baseline covariates. Missing data will be handled via Mixed Model for Repeated Measures (MMRM), with sensitivity analyses using ANCOVA on datasets imputed by multiple imputations (MI) and Last Observation Carried Forward (LOCF).

2) Secondary efficacy endpoints

Changes in NRS for low back pain, 100 mm Pain Visual Analog Scale (VAS), Roland-Morris Disability Questionnaire (RMDQ), EuroQol 5-Dimension 5-Level (EQ-5D-5L), Health Information National Trends Survey (HINT-8), Global Perceived Effect (GPE), Patient Health Questionnaire-15 (PHQ-15), economic measures, and Kidney Yin Deficiency Pattern Identification Questionnaire (DSKI) scores will be analyzed using a Linear Mixed Model with baseline covariates. Missing data will be managed via MMRM, with ANCOVA sensitivity analyses using MI and LOCF. Non-inferiority testing, with margins of −1.75 (NRS) and −10 (ODI), will be conducted if superiority is not achieved, considering herbal medicine non-inferior if the 95% confidence interval lower bound does not exceed these margins.

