### Safety

2.9

The investigator will evaluate and document all adverse events (AEs) and serious adverse events (SAEs) during the study, adhering to WHO intensity classification guidelines, with non-covered AEs graded as: grade 1 (mild, transient, no treatment or activity limitation); grade 2 (moderate, mild to moderate activity limitation, may require treatment and recovery); or grade 3 (severe, marked limitation, requiring medical intervention or hospitalization). AEs and SAEs will be recorded in the Case Report Form (CRF) using medical terminology or detailed symptoms/signs, with pre-existing conditions noted in screening history and pre-treatment AEs documented separately. Emergency responses include oral NSAIDs for sudden pain exacerbation and immediate cessation, first aid, and emergency referral for acupuncture-related AEs (e.g., pneumothorax, bleeding, fainting). SAEs, except minor gastrointestinal discomfort (e.g., heartburn from herbal medicine), will be reported to the principal investigator or coordinator per regulations within 30 days post-trial. The CRF AE log will capture symptoms, onset, intensity, course, actions, outcome, and causality, with ongoing AEs reviewed, resolved AEs updated, escalating AEs logged anew, and treatment adjustments documented.

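### The exploratory non-inferiority statement follows the ITT set by default, and nothing in the plan lets a contradicting per-protocol result stop it

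*Protocol article*

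**What the plan says.** All references are to the protocol article.

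- **Hierarchy of sets (2.7).** Efficacy is analysed in both sets, "with ITT as the primary analysis and PP as supportive". No exception is made for non-inferiority.
- **ITT set (2.7).** "The ITT population includes all randomized participants receiving at least one dose of herbal medicine or one traditional Korean medicine (TKM) session".
- **PP set (2.7).** "The PP population comprises ITT participants with ≥70% herbal medicine compliance or ≥7 TKM sessions". The definition says nothing about co-treatment or rescue.
- **Non-inferiority (2.7.2).** "Non-inferiority testing, with margins of −1.75 (NRS) and −10 (ODI), will be conducted if superiority is not achieved". The decision compares the lower 95% confidence limit with the margin, and no analysis set is named.
- **Status of non-inferiority (2.3).** It is described as secondary, exploratory, hypothesis-generating and underpowered. The margin and the two-sided 95% interval are to be reported.
- **Co-treatment (2.5.3).** "there will be no restrictions on concomitant therapies for LBP or radiculopathy symptoms during the study period". Section 2.9 adds: "Emergency responses include oral NSAIDs for sudden pain exacerbation".
- **Withdrawal (2.8).** Grounds include "herbal medicine adherence below 70% across 5 weeks or fewer than six usual care sessions attended". Follow-up assessments may continue with consent.

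**The concern.** For superiority, letting ITT decide is cautious, because any dilution of the contrast works against the claim. For non-inferiority the same dilution works for it. If herbal medicine as taken is worse than usual care, and participants who stop or take little of their assigned treatment pull the two means together, the ITT interval moves away from the margin. The usual safeguard is to ask whether the PP set tells the same story. Here PP is analysed, but it has no part in the decision.

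The fallback may well be used. At the design effect of 0.5 SD, superiority power with 33 per arm is about 53%, so each endpoint would reach the fallback nearly half the time even if the design assumption were true. If the arms are equal, the chance of passing the ODI rule is about 98% at SD 10 and 53% at SD 20. Non-inferiority could therefore become the trial's main positive statement, and the abstract and 2.7.2 announce it without the exploratory label.

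**Working it through.** **Inputs from the protocol article.** Margins are 1.75 (NRS) and 10 (ODI), from 2.7.2. The 95% interval is two-sided, so the test is one-sided at 2.5%. Evaluable participants number 33 per arm (Table 2). Section 2.3 gives SD 10 and difference 5, but does not tie them to NRS or ODI.

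**Assumptions.** ODI SD is 10, 15 or 20, and NRS SD is 2.0 or 2.5. The ITT contrast is smaller than the contrast among adherent participants by a fraction f of 10%, 20% or 30%. The documents give no adherence rate from which f could be derived. The difference is oriented so that negative values disfavour herbal medicine, and the rule is read as requiring the lower limit to lie above the negative margin.

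**The plan's own figure.** The stated inputs do not reproduce 33 per arm: 2 × (1.960 + 0.842)² × (10/5)² = 62.8, so 63 per arm. That is a separate matter. I use 33 because it is the evaluable number the plan states. Power at 33 is Φ(5/2.462 − 1.96) = Φ(0.07) = 0.53, with standard error 10 × √(2/33) = 2.462.

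**False-claim rate.** Set the true deficit among adherent participants equal to the margin M. The ITT deficit is then M(1 − f), and

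P(claim) = Φ( fM / SE − 1.96 ), with SE = SD × √(2/33).

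For ODI at SD 10 and f = 10%: Φ(1/2.462 − 1.96) = Φ(−1.55) = 0.060. The other cells follow in the same way:

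| Outcome, SD | SE | f = 0 | 10% | 20% | 30% |
|---|---|---|---|---|---|
| ODI, 10 | 2.462 | 2.5% | 6.0% | 12.6% | 22.9% |
| ODI, 15 | 3.693 | 2.5% | 4.6% | 7.8% | 12.6% |
| ODI, 20 | 4.924 | 2.5% | 3.9% | 6.0% | 8.8% |
| NRS, 2.0 | 0.492 | 2.5% | 5.4% | 10.6% | 18.6% |
| NRS, 2.5 | 0.615 | 2.5% | 4.7% | 8.2% | 13.4% |

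**If the arms are equal**, the chance of passing on ODI is Φ(10/2.462 − 1.96) = 0.98 at SD 10 and Φ(10/4.924 − 1.96) = 0.53 at SD 20.

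**Session rules side by side.** PP needs at least 7 sessions (2.7). Withdrawal applies below six (2.8). Frequency may be 1–3 per week, with at most 10 sessions (2.5.2 and Table 1, footnote 12). One session a week for the 5-week course gives 5 sessions: within the permitted frequency, outside PP, and meeting the withdrawal criterion. Exactly six sessions is neither grounds for withdrawal nor enough for PP.

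**The case against.** The strongest objection concerns the target of estimation. This is a pragmatic comparison of strategies with co-treatment open by design. If the question is the effect of assignment under routine care, non-adherence and co-treatment belong to what is being compared, and the ITT test keeps its 2.5% error. This stands. A reader might infer that the non-inferiority test has an inflated type I error outright. The documents do not support that, because the inflation exists only relative to an effect among adherent participants.

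A reader might also infer that a confirmatory claim rests on ITT alone. Section 2.3 says otherwise: non-inferiority is exploratory and underpowered. PP is analysed as well, and the Background plans sensitivity tests for adherence and treatment frequency. That lowers the stakes, but none of it tells the analyst what to conclude if ITT and PP disagree. That ITT decides is itself an inference from the general hierarchy, though it is the only reading the current text offers. Nor is this simply detail left to an analysis plan, since the article itself fixes the sets, their order, the margins and the rule.

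Three further points have force. Requiring one dose or session removes never-treated participants, so this set is less diluted than all randomised participants. Dilution towards equality is not assured: if herbal medicine is worse than usual care but better than nothing, stopping it early could widen the deficit, and co-treatment narrows the gap only if the worse arm uses more of it. Finally, it is tempting to present PP agreement as the cure for rescue and co-treatment. It is not, because PP selects on adherence alone and keeps co-treated participants. PP also has its own selection: if control patients with few sessions are those doing well, excluding them would favour herbal medicine. Even so, requiring both sets to pass can never make a claim easier than ITT alone.

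**Conclusion.** The point holds as a gap in the decision rule for an exploratory analysis. As written, a PP result that fails to exclude the margin would not stop a non-inferiority statement based on ITT. Relative to the effect among adherent participants, the false-claim rate is about 6–23% for ODI at SD 10, 4–9% at SD 20, and 5–19% for NRS at SD 2.0–2.5, against 2.5%. These figures assume 33 per arm, a true deficit exactly at the margin, and shrinkage of 10–30%. The shrinkage and the SDs by scale are not given in the documents, so the figures illustrate the sensitivity and do not predict it. For a treatment-policy contrast the rate stays at 2.5%.

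**What to change.** Add to 2.7.2: the exploratory non-inferiority conclusion is drawn only if the margin is excluded in both the ITT and the PP set; both intervals are reported; if they disagree, no claim is made; ITT remains the deciding set for superiority.

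State alongside it that agreement with PP does not remove the influence of unrestricted co-treatment. The 7-session PP cut-off, the six-session withdrawal criterion and the permitted session frequency must also be reconciled, since the PP set now carries weight in the decision.

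The cost is small: one sentence and an analysis already planned, with no change to the superiority test. The downside is that non-inferiority becomes somewhat harder to claim.
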